### 2.3. Study Design

The study will utilise a randomised design, compared to standard treatment intervention. Figure 3 shows the flowchart of this study. It will have two arms: treatment of embedded sand-flea infestations with 5% sodium carbonate, versus dimeticone. Randomisation will be performed according to treatment. A non-inferiority design is chosen, since it would be unethical to withhold an existing treatment that has demonstrated efficacy. This study will not measure any environmental intervention; therefore, we can measure only efficacy, not effectiveness. All participants will receive both treatments, one on each foot. Therefore, it is not possible to blind participants and interveners to treatment-group assignments. The study will be conducted during the dry season, when the prevalence of tungiasis is known to be at its peak, and at a time not impacted by holidays.

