### 2.6. Outcome Measures

The primary endpoint is the cure rate on day seven, following treatment with either 5% sodium carbonate solution or dimeticone. Embedded fleas will be assessed using a digital handheld microscope at the baseline, and on days 3, 5, and 7 for four signs of viability: expulsion of eggs, excretion of faecal thread, excretion of faecal liquid, and pulsations/contractions. An embedded flea will be considered non-viable if none of the four signs of viability is detected during 15 min of observation.

Secondary endpoints are adverse effects (nausea/vomiting, arthralgia, fever, headache, fatigue/malaise, myalgia, and chills), acute pathology scores (assessing pain, itching, erythema, warmness, oedema, desquamation, fissure, suppuration, ulcer, abscess, and lesions in clusters), and differences in feeling and ease of children during the 7-day period after the treatments. Each participant will also be asked to rate their experience of pain and itching using a quick help-sheet with illustrations. An inflammation score [15] will be used for this assessment.

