### 3.2. Randomisation, Allocation, and Blinding

All study participants will receive 5% sodium carbonate and dimeticone, with one treatment per foot. Randomisation will be carried out at the treatment level and not the individual level. Trained nurses will perform the intervention. It is not possible to blind the intervener administering the treatment because 5% sodium carbonate will require soaking the foot, whereas NYDA^®^ will be applied directly to each lesion. As the two treatments will not change the skin colour of the feet, the principal investigator will be a blinded observer.

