## 4. Expected Results

Based on the results of previous studies, the treatment of tungiasis is not sustainable for rural communities. In this study, the primary endpoint will be the cure rate on day 7, following treatment with either 5% sodium carbonate solution or dimeticone, while the secondary endpoints will be differences in adverse effects and acute-pathology scores on day 7, as well as differences in feeling and ease on day 7. Therefore, this study can contribute toward designing a locally sustainable management-cycle that will improve the cure rate, reduce the scores of adverse effects and acute pathology, and sustain the acceptable local treatment for children in Kenya. We hope to help adopt new treatments into the national guidelines of Kenya. The treatment will be cheaply available locally and accessible to poor families suffering from tungiasis in this study area.

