### 4.1. Statistical Analysis

For the primary outcome, logistic regression analysis (stepwise regression) will be performed, because it is binary. Since all secondary outcomes are score data, they are continuous measures; thus, analysis of covariance will be performed using two variables (sex (male or female) and footwear use (shoes or sandals)) as covariants. This is because previous studies have shown that the male sex is a risk factor for tungiasis, and that the thickness of the skin of the foot may change depending on whether sandals are used, which may affect the penetration of the treatment [32]. We will use generalized estimating equations for side effects such as pain and itching, to consider relative risks. The per-protocol set, which analyses only subjects who adhere to treatment, is more likely to show superiority or a significant increase in risk, while the intention-to-treat analysis is more likely to show non-inferiority with or without significant differences. Therefore, a per-protocol approach will be adopted for this non-inferiority study. All data will be analysed using EZR version 1.60 (Jichi Medical University Saitama Medical Center, Saitama, Japan). Missing values will be imputed using the multiple-imputation method. For the main analysis, we will use one-sided *p*-values at an *α* = 0.025 level of significance; for others, we will use two-sided *p*-values at an *α* = 0.05 level of significance.

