### 4.4. Adverse Events/Effects

All adverse events, whether serious or non-serious, will be recorded until day 7, which is the end of the study, after the participant and his/her caregivers have provided assent and consent and enrolled in the study. If a participant experiences an adverse event after the informed-assent and consent forms are signed, but the participant has not started to receive the study intervention, the event will be reported as unrelated to the study treatments. A serious adverse event for this study is defined as any untoward medical occurrence that is believed by the investigators to be causally related to the study treatments and results in any of the following: a life-threatening condition with an immediate risk of death, severe or permanent disability, and prolonged hospitalisation. Serious adverse events occurring after a participant discontinues the study will not be reported unless the investigators feel that the event may have been caused by the study drugs or a protocol procedure. The investigators will determine the relatedness of an event to the study treatment, based on a temporal relationship to the study treatment and whether the event is unexpected or unexplained given the participant’s clinical course, previous medical conditions, and concomitant medications. All adverse events will be assessed as part of routine monitoring. Any adverse event that can be attributed to the intervention will be specified as a secondary outcome. However, we cannot know which treatment might cause adverse effects with general symptoms such as fever and high blood-pressure, since all participants will receive both treatments. Therefore, those general symptoms will be checked for the safety of the study and to provide information for a doctor to judge whether to continue the research; other acute pathologies, such as skin symptoms, can be analysed by each treatment.

The study will carefully evaluate the safety and harm of the interventions, specifically, the quality and proper preparation of 5% sodium carbonate and dimeticone, and the procedure for applying these solutions to the participants’ feet. The principal investigator or co-investigators will follow any clinically significant abnormalities until resolution or until a clinically stable endpoint is reached. 

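### The ANCOVA for secondary scores ignores the split-foot pairing, and the promised treatment difference in systemic adverse effects conflicts with the article's own statement that they cannot be attributed

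*Protocol article*

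**What the plan says.** **Design.** Protocol article, Section 2.3: "All participants will receive both treatments, one on each foot". Section 3.2 adds: "Randomisation will be carried out at the treatment level and not the individual level". The envelopes in Section 3.1 decide only which foot gets which treatment, so every treatment contrast is a contrast within a child.

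**Analysis of secondary outcomes.** Section 4.1 reasons: "Since all secondary outcomes are score data, they are continuous measures". It concludes that "analysis of covariance will be performed using two variables (sex (male or female) and footwear use (shoes or sandals)) as covariants". The reasons given are that boys are at higher risk of tungiasis and that sandal use may alter skin thickness and so penetration. No child or pair term and no baseline score is named. The next sentence reads: "We will use generalized estimating equations for side effects such as pain and itching, to consider relative risks". It does not say what the cluster is. Section 2.6 lists pain and itching as the first two components of the acute pathology score.

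**Adverse effects.** Objective 2 in Section 2.1 is to assess safety through incidence. Section 2.6 begins its list of endpoints: "Secondary endpoints are adverse effects (nausea/vomiting, arthralgia, fever, headache, fatigue/malaise, myalgia, and chills"; all seven are systemic. Section 4 states that "the secondary endpoints will be differences in adverse effects and acute-pathology scores on day 7". Section 4.4 concedes that "we cannot know which treatment might cause adverse effects with general symptoms", because every participant gets both treatments. It assigns general symptoms to safety checking and says that skin symptoms can be analysed by treatment.

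**The concern.** A split-foot design earns its precision by removing differences between children from the treatment comparison. An ANCOVA whose only other terms are sex and footwear treats a child's two feet as two independent observations and gives that precision away. Because the article fixes the covariates at two and argues for them, this is a stated choice and not a detail left to an analysis plan. The comparison of acute pathology scores (objective 3) depends on it, as does any comparison of feeling and ease (objective 4) that is scored per foot.

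The second part is a contradiction. A between-treatment difference is promised for an endpoint made up only of symptoms that, on the article's own account, cannot be assigned to either treatment. The stated data type is also wrong for it: incidence counts children with or without an event and is not a continuous score.

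**Working it through.** **No figure of the plan to reproduce.** The article gives no sample size, power or correlation for any secondary outcome. The ICC of 0.5 in Section 2.8 refers to lesions in the primary sample size, so it is not borrowed here as the correlation of scores. The correlation ρ between a child's two foot scores is an assumption, shown over a range. It is the correlation left after sex and footwear.

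**Step 1: what the covariates do.** With one score per foot, each child contributes one foot to each arm, so sex has the same distribution in both arms, and so in practice does footwear. Neither can confound the contrast or shift the estimate. A simulation with 230 children (460 lesions per arm at two per foot) and 1,000 runs confirmed this: adding both terms changed the treatment estimate by less than 1e-14.

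**Step 2: standard error, one score per foot.** For N children with score variance σ²:

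- true variance of the treatment difference: 2σ²(1−ρ)/N
- variance used when feet are taken as independent: 2σ²/N
- ratio of standard errors: 1/√(1−ρ)
- actual two-sided error of a nominal 5% test (the level in Section 4.1): 2[1−Φ(1.96/√(1−ρ))]
- power where a paired analysis would have 80%: Φ(1.96 + 0.84 − 1.96/√(1−ρ))

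| ρ (assumed) | SE ratio | 1.96/√(1−ρ) | Actual error | Power, if paired = 80% |
|---|---|---|---|---|
| 0.3 | 1.20 | 2.34 | 1.9% | 68% |
| 0.5 | 1.41 | 2.77 | 0.6% | 51% |
| 0.7 | 1.83 | 3.58 | 0.03% | 22% |

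The simulated error at ρ = 0.3 was 0.019 for the ANCOVA and 0.048 for the paired analysis; at ρ = 0.5 it was 0.007 and 0.052.

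**Step 3: if the lesion is the unit.** Sections 2.8 and 3.1 allow one to five lesions per foot, and the article does not say whether scores are per foot or per lesion. With m lesions on each foot, correlation ρw within a foot and ρb between a child's feet, the true variance divided by the variance assumed under independence is 1 + (m−1)ρw − mρb. This exceeds 1 when (m−1)ρw > mρb. For illustration only, with Section 2.8's cluster size of 2 and 0.5 as ρw, the condition is 0.5 > 2ρb, that is ρb < 0.25. The test would then reject too often. With unequal lesion counts on the two feet, the balance in Step 1 would also no longer be exact.

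**Step 4: adverse effects side by side.**

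| Section | Content |
|---|---|
| 2.1 | Safety assessed by incidence |
| 2.6 | Seven symptoms, all systemic |
| 4 | Treatment differences in adverse effects are an endpoint |
| 4.1 | All secondary outcomes are continuous scores |
| 4.4 | General symptoms cannot be assigned to a treatment; skin symptoms can |

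A systemic event belongs to a child who received both treatments, so it has the same value under each. No difference can be estimated. Section 4.4 is consistent with the design; Section 4, read with the list in Section 2.6, is not.

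**The case against.** **Correlation is not ignored everywhere.** A reader might infer that the plan has no method for correlated data. The GEE sentence does not support that: GEE may handle pain and itching properly. This stands, and limits the point to the ANCOVA. It does not remove it. The sentence covers some symptoms only, names no cluster, and leaves pain and itching under two methods, since they are also part of the score sent to ANCOVA.

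**Attribution is not lost altogether.** A reader might infer that no adverse effect can be compared. Section 4.4 says the opposite for skin symptoms, and makes events attributable to the intervention a secondary outcome. Several local signs (erythema, oedema, ulcer and others) are captured by foot in the acute pathology score. Objective 2 also says assess where objectives 1 and 3 say compare. What remains is the clash between Sections 2.6 and 4 on one side and Section 4.4 on the other.

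**The covariates do no harm.** Correct: they leave the estimate unchanged, and the article gives a reason for footwear. Removing them is a matter of preference. Leaving out the baseline score costs efficiency and causes no bias in a randomised comparison.

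**The size is assumed.** Also correct: ρ is not in the article, and the table needs one score per foot.

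**Adverse effects may be meant as scores.** Section 4 does speak of adverse-effect scores, but objective 2 is incidence, and the article does not reconcile the two.

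**Conclusion.** The point holds in limited form. The ANCOVA as stated does not account for the pairing that the design creates. For one score per foot and positive correlation, its standard errors are too large by a factor of 1.20 to 1.83 over the assumed range of ρ from 0.3 to 0.7. The effect is lost power and over-wide intervals. A biased estimate or excess false positives should not be inferred for foot-level scores; the second becomes possible only if lesions are the unit, which the article leaves open.

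The contradiction over systemic adverse effects, and their description as continuous scores, rest on the text alone and need no assumption. The primary endpoint is not touched by either part. The changes should be made, but the trial's main conclusion does not depend on them.

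**What to change.** 1. In Section 4.1, state that the acute pathology score is analysed at day 7, one score per foot, with a within-child model: a random effect for child, GEE clustered on child, or the paired difference between feet. Adjust for that foot's pre-treatment score where it is recorded. If earlier visits are included, add a treatment-by-visit term so that the day-7 contrast remains the target. Sex and footwear may stay, but they do not stand in for the pairing.
2. Say which method applies to pain and itching, and name the child as the GEE cluster.
3. Bring Sections 2.6, 4 and 4.1 into line with Section 4.4: describe systemic events per child without a between-treatment test, and compare only local skin events by foot, as paired binary data.
4. Remove the statement that every secondary outcome is a continuous score.

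The cost is mainly analysis wording. Sample size and treatment do not change. The one practical check is whether the record form captures each foot's score before application.

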### 2.8. Sample-Size Calculation

Based on the hypothesis, there is a difference between treatment with 5% sodium carbonate, with a 70% cure rate [14], and dimeticone, with a 78% cure rate [15]. Although it depends on the result of the pilot study, we would like to calculate the sample size assuming that both cure rates are 80%. The sample size was calculated using the method proposed by Schoenfeld [31], assuming a non-inferiority margin of 10% (δ = 0.1) and that the true mean cure-rates of the treatment agent (sodium carbonate) and the active control (NYDA^®^) are 80% (pT = 0.80) and 80% (pC = 0.80), respectively. We calculate the optimum sample needed to achieve 90% power (1 − β = 0.9) at the 5% level of significance (α = 0.05) with equal allocation (*k* = 1) for demonstrating non-inferiority for the clinical-cure assessment of efficacy. Since one to five lesions per foot will be studied per participant, the intra-class correlation coefficient (ICC) (1, *k*) with *k* = 2–5, would be used to evaluate the intra-rater reliability of the values, yielding an estimated ICC = 0.5. As the cluster size is two, the design effect is calculated as 1 + (2 − 1) × 0.5 = 1.5. A total of 920 (460 per arm) lesions will be recruited, considering a 10% rate of loss to follow-up. 

Before conducting this non-inferiority trial, a cohort study will be conducted as a pre-study. The sample size is estimated to have an 80% efficacy rate, absolute precision is 10%, and therefore 62 lesions are enrolled in each concurrent, parallel-treatment cohort.

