### 3.5. Data Collection and Storage

Data will not be collected on the names and affiliations of the participants. If they wish to discontinue the interview, observation, and treatment, their decision will be respected without any objections. Participation of school children in this study is totally voluntary. Since this is a school-based study, consent will first be obtained from each school. Informed consent will then be obtained from each participant, in accordance with the Ottawa Statement, an international guideline for cluster-randomised trials. For lesions not studied, dimeticone will be applied later, if desired. The area to be observed will be marked with an oil-based pen and photographed with a smartphone. Video recordings with a smartphone will be made only at the time of intervention, to confirm the intervention method. During the treatment, skin symptoms will be monitored until the final decision on the 7th day, using a checklist. Lesions will be examined and staged according to the Fortaleza classification [2], and counted (live/dead). The cure rate will be calculated at each stage, and significant differences at each stage will be tested. Participants will be observed and queried about adverse effects, and the severity score will be used to assess symptoms of acute tungiasis, including pain and itching. Feeling and ease of each treatment will be assessed using a questionnaire. Trained nurses will monitor the participants, and interviews will be conducted under the guidance of a medical doctor at treatment initiation and during the final decision. 

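### Section 4.1 sends the graded pain and itching ratings to a relative-risk GEE, which implies a yes/no event and conflicts with the score-based analysis stated for the same outcomes

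*Protocol article*

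**What the plan says.** Section 2.6 of the protocol article lists pain and itching among the eleven items of the acute pathology score, not among the adverse effects. It adds: "Each participant will also be asked to rate their experience of pain and itching using a quick help-sheet with illustrations". Section 3.5 says that "the severity score will be used to assess symptoms of acute tungiasis, including pain and itching".

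Section 4.1 then makes two statements about analysis. The general one is: "Since all secondary outcomes are score data, they are continuous measures; thus, analysis of covariance will be performed", with sex and footwear as covariates. The specific one, shortly after, is: "We will use generalized estimating equations for side effects such as pain and itching, to consider relative risks". No event or cut is attached to the relative risk, and neither analysis is named as the main one for these symptoms.

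On design, section 2.3 states: "All participants will receive both treatments, one on each foot". Every comparison of the treatments on a foot-level rating is therefore a comparison within the child. GEE is the only method for correlated data that section 4.1 names.

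**The concern.** Pain and itching are ratings, yet the one analysis that names them uses an effect measure for yes/no events. To obtain a relative risk, each rating must be reduced to present/absent or to above/below some level.

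The reduction matters most with an any-versus-none event. A child with severe pain on one foot and mild pain on the other counts as having pain on both, so the pair contributes no difference. Irritation from a treatment that raises severity without changing presence is missed in the same way. Children are enrolled because they show symptoms (2.5), and the Introduction links constant itching and pain to poor concentration at school. Differences in degree are therefore of interest as well as differences in presence.

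Two incompatible scales for the same symptoms, with neither named as main, also leave the choice open until the data are seen.

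**Working it through.** **1. The passages side by side.**

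| Place | Pain and itching are | Analysis |
|---|---|---|
| 2.6 | rated on an illustrated sheet; 2 of 11 items in the pathology score | – |
| 3.5 | part of a severity score | – |
| 4.1, general sentence | continuous scores, like all secondary outcomes | analysis of covariance; sex, footwear |
| 4.1, specific sentence | side effects | GEE, relative risks |

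The last two rows cannot both describe the main analysis of the same rating.

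**2. Does the covariance analysis cover the gap?** Only in part. The pathology score pools pain and itching with 11 − 2 = 9 other items, so a difference in felt symptoms can be diluted. The stated covariates do not use the pairing: sex is the same for both feet of a child, and no child term is named.

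**3. Is there a figure in the plan to reproduce?** Not for these outcomes. The phrase "to achieve 90% power (1 − β = 0.9" in 2.8 concerns cure only. I use the 460 lesions per arm solely to count children: at 5, 3 or 2 lesions per foot, 460/5 = 92, 460/3 ≈ 153 and 460/2 = 230. The level is two-sided 0.05 (4.1: "for others, we will use two-sided").

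**4. Assumptions, none from the documents.** One rating per foot; latent-normal severity; within-child correlation 0.5; one foot shifted by a constant; 3 to 11 levels with various distributions.

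**5. Formula.** For small shifts, with cut points c_j on the latent scale and φ the normal density:
- information in the mean score: (Σφ(c_j))² / E[(S₁ − S₂)²]
- information in cut j: φ(c_j)² / P(the two feet fall on different sides of c_j)
- efficiency e = best cut information / score information
- power at the best cut, when the graded analysis has 80%: Φ((1.960 + 0.842)·√e − 1.960)

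**6. Worked case: four evenly used levels, correlation 0.5.**
- Cuts at −0.674, 0 and 0.674, so Σφ = 0.318 + 0.399 + 0.318 = 1.034.
- E[(S₁ − S₂)²] = 1.405, so score information = 1.034²/1.405 = 0.761.
- The middle cut is best. The feet differ with probability 1/3, so its information is 0.399²/0.333 = 0.477.
- e = 0.477/0.761 = 0.627, and power = Φ(2.802 × 0.792 − 1.960) = Φ(0.258) = 60.2%. The loss is 19.8 points.

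Simulation agrees. With 153 children and a 0.25 SD shift, power is about 77% on the rating, 55 to 57% at the best cut, and about 45% for any versus none.

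**7. Range at correlation 0.5, graded analysis at 80% unless stated.**

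| Assumed distribution | e | Best-cut loss (points) |
|---|---|---|
| 11 even levels | 0.531 | 26.8 |
| 6 even levels | 0.568 | 24.0 |
| 4 even levels | 0.627 | 19.8 |
| 50/30/15/5% | 0.716 | 14.1 |
| 70/15/10/5% | 0.846 | 6.9 |
| 85/10/5%, simulated, 0.3 SD, 153 children | – | 60% vs 56%: 4 |
| 85/10/5%, simulated, 0.3 SD, 230 children | – | 79% vs 76%: 3 |

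For 85/10/5% the closed form gives e = 0.94 and Φ(2.802 × 0.970 − 1.960) = Φ(0.756) = 77.5%, a loss of 2.5 points. The lower end is therefore soft.

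**8. Sensitivity to correlation.** Over ten distributions (not including 85/10/5%), the best-cut loss at 80% power is 3.2 to 16.6 points at correlation 0, 4.6 to 21.7 at 0.3, and 11.3 to 34.6 at 0.7. The loss grows with correlation because cutting the rating also weakens the within-child correlation that the split-foot design relies on.

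**The case against.** **A graded analysis is already planned.** The general sentence in 4.1 covers all secondary scores, and the pathology score contains both symptoms. Nothing says the relative risk replaces it. A reader might infer that pain and itching will be analysed only after a yes/no cut. The documents do not support that: the cut is inferred from the effect measure and is nowhere stated. What remains is that the planned score analysis is pooled and names no child term, while the analysis naming these symptoms is on the wrong scale for a rating.

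**The sentence may mean incidence of side effects.** Objective 2 in section 2.1 is the incidence of adverse effects, there is an adverse event form (3.4), and incidence is binary without cutting any rating. This reading is possible. Against it, the adverse-effect list in 2.6 omits pain and itching and places them in the pathology score, and 3.5 treats them as symptoms of acute tungiasis.

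**The power figures are the reviewer's.** This stands. The article gives no number of levels, distribution, correlation or effect size, and 2.6 does not say the rating is taken per foot. A reader might infer a firm loss of 7 to 27 points that never falls below 5. That does not hold: with most feet symptom-free, the best cut is any versus none and loses only a few points. A constant latent shift also favours the mean score.

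**The cut is detail for the analysis plan.** The missing cut alone would be. The conflict between two stated analyses is not, because the article itself fixes both.

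**Conclusion.** The point holds as a conflict within section 4.1 and a poorly chosen effect measure for rated symptoms; neither part needs an assumed number. The size of the power loss is conditional. With paired latent-normal ratings, one per foot, and correlation 0.5, the best cut loses roughly 4 to 27 points, and slightly less than 4 in some settings where most feet have no symptom. Lower correlation reduces the loss and higher correlation increases it. No power is claimed in the plan for these outcomes. They are secondary, and the cure-rate comparison is untouched. The change is worth making but is not critical.

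**What to change.** In section 4.1, replace the relative-risk sentence for pain and itching. State that the main analysis of each is a GEE with the child as cluster, fitted to the rating itself: either an identity link, giving the mean between-foot difference, or a cumulative logit, giving a common odds ratio. Choose one in advance. Adjust for that foot's pre-treatment rating where ratings were taken per foot. Keep any relative risk as a supportive summary with a cut fixed beforehand. If the sentence was meant for the incidence of side effects, say so and define the event separately from the rating.

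The cost is a sentence or two of analysis wording, with no new visits or participants. The small downside is an effect measure less familiar than a relative risk, which the supportive summary offsets.
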